### Data analyses

The design of the statistical analysis is based on previous studies of literature relating to clinical and placebo-controlled trials using tDCS [17, 30, 90, 91]. The intention-to-treat analysis will be used; however, high or differential rates of missing data between treatment arms/sides may indicate a departure from this assumption and may lead to bias [92]. Thus, a sensitivity analysis will be performed with different allocation procedures to verify the strength of the data. The best strategy resulting from the comparison of the following methods will be chosen: last observation carried forward, complete case analysis, likelihood-based methods, and multiple imputation [93]. As pointed out by White et al. [94] in the intention-to-treat analysis strategy, the main focus in the analysis of choice should be the plausibility of its assumptions, while the inclusion of all randomized individuals is a requirement only for sensitivity analysis.

Multivariate imputation by chained equations (MICE, the R Foundation for Statistical Computing, Vienna, Austria) and SPSS Ver.20.0 (SPSS Inc., Chicago, IL, USA) software will be used.

Regarding sociodemographic and clinical characteristics at the baseline, for continuous variables, information on the variability will be presented for example, mean and standard deviation). If groups are similar to each other, descriptive data analysis will be performed. However, if important differences are found, regression analysis will be used to evaluate these data to estimate the effects of covariates with the variables of interest.

Regarding clinical outcomes, the primary outcome will be analyzed with analysis of mean change scores (MCS) to the total score of BI. The MCS will be evaluated in three ways: change occurred between the post and pre-test (T1-T0); between endpoint and pre-test (T2-T0); between the endpoint and post-test (T2-T1). The baseline as covariate will be used to identify potential differences between the groups by analysis of covariance (ANCOVA) [95].

Finally, the effect sizes and confidence intervals of change scores will be calculated using Cohen’s *d*, using the Hedges correction, with values of 0.20, 0.50, and 0.80, reflecting small, medium, and large effects, respectively [96]. For all variables of the secondary outcomes, the same analysis strategy will be used. Non-parametric tests will be performed if some of the outcomes do not meet the conditions necessary for parametric analysis.

Regarding safety, deleterious adverse and cognitive effects will be recorded/computed in terms of the proportion in each group, in each time period (T0, T1, and T2), and will be analyzed by the Fisher exact test.

Bias-generating will be tested. The statistical model used for blinding effectiveness was based on the study of Brunoni et al. [97]. The chi-square test or Fisher’s exact test will be used to assess if tDCS blinding guessing was beyond chance for patients, external judges, and trialists. Paired *t*-tests will be used to compare the rate of their guessing according to the Likert scale. Logistic regressions exploring the factors associated with “correct blinding guessing” (that is, participants who correctly guessed their allocation group) will be performed. The factors will be clinical response, high guessing confidence (scores 4 or 5 on the Likert scale), and adverse effects.

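### The primary missing-data method is left to be chosen after comparing four candidates, with no ranking, default or pre-unblinding deadline, so LOCF or complete case could become the main analysis under an intention-to-treat label

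*Protocol article*

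**What the plan says.** All the relevant text is in the first paragraph of Data analyses in the protocol article.

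- The label and its caveat: "The intention-to-treat analysis will be used; however, high or differential rates of missing data between treatment arms/sides may indicate a departure from this assumption".
- The response to that caveat: "a sensitivity analysis will be performed with different allocation procedures to verify the strength of the data". Given what follows, allocation here appears to mean imputation.
- The selection rule: "The best strategy resulting from the comparison of the following methods will be chosen: last observation carried forward, complete case analysis, likelihood-based methods". The sentence ends by adding multiple imputation.
- The guidance on choosing: "the main focus in the analysis of choice should be the plausibility of its assumptions".
- The role of the full randomised set: "the inclusion of all randomized individuals is a requirement only for sensitivity analysis".

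The next paragraph names MICE and SPSS as software, without making multiple imputation the primary method. The primary outcome is the change in total Barthel index over T1-T0, T2-T0 and T2-T1, with a baseline-adjusted ANCOVA. The secondary outcomes follow the same strategy.

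**The concern.** A sensitivity analysis fixes one primary analysis and shows how far its answer moves under other assumptions. Here the alternatives are compared and one of them becomes the analysis. The four methods make different assumptions about values nobody observed, and comparing them on the trial's own data cannot show which assumption holds. Without a ranking or a deadline, the choice can be made by someone who has seen what each method does to the treatment effect. The p-value and confidence interval would then ignore that selection.

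Two of the candidates also sit badly with the intention-to-treat label. Complete case omits randomised participants, which the paragraph allows because it requires everyone only in the sensitivity analysis. LOCF gives zero change to anyone lost before T1. In a subacute population receiving daily CIMT, where both arms may well improve, that penalises the arm with more early loss.

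**Working it through.** **Inputs from the protocol article**
- Sample size: difference 10 points, SD 7, power 90%, alpha 0.05, 12 per group raised to 20.
- Study limitations, on the cited depression trial: 9/120 = 7.5% lost at three weeks and 17/120 = 14.2% at six weeks.
- Loss allowance implied by the enrolment: 1 - 12/20 = 40%.

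**The plan's own figure.** With d = 10/7 = 1.43 and a two-sided two-sample t-test, power is 0.890 at 11 per group and 0.917 at 12. So 12 reproduces, and 12/(1 - 0.40) = 20. The sample size is not in dispute.

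**Assumptions not in the documents**
- Baseline SD 15; SD of change 7; correlation 0.6 between the T1 and T2 changes.
- Under the null, both arms gain 7 points by T1 and 10 by T2.
- Dropout is monotone and completely random within arm, with half of it before T1.
- T2-T0 is analysed by baseline-adjusted ANCOVA with 20 per arm, two-sided at 0.05. The likelihood method is a factored normal likelihood; multiple imputation uses 20 imputations.

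**Type I error, 4,000 null trials per row**

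| Dropout (control / active) | LOCF | Complete case | Likelihood | MI | Most favourable of four |
|---|---|---|---|---|---|
| 7.5% / 7.5% | 0.054 | 0.052 | 0.052 | 0.052 | 0.069 |
| 14.2% / 14.2% | 0.047 | 0.050 | 0.049 | 0.048 | 0.078 |
| 25% / 25% | 0.051 | 0.050 | 0.044 | 0.042 | 0.085 |
| 40% / 40% | 0.045 | 0.047 | 0.044 | 0.040 | 0.087 |
| 25% / 5% | 0.082 | 0.055 | 0.049 | 0.046 | 0.113 |
| 40% / 10% | 0.128 | 0.047 | 0.043 | 0.040 | 0.159 |

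With equal dropout, any single method fixed in advance holds its level to within simulation error or slightly below it. The excess comes from the freedom to choose. A separate simulation with correlations of 0.8, 0.7 and 0.8 and without the likelihood method gave 0.066 and 0.065 at 7.5% and 14.2%, and 0.085 at 40%. A 20,000-trial repeat of the table's set-up with only LOCF and complete case gave 0.066, 0.073 and 0.081 at 7.5%, 14.2% and 40%. In that repeat LOCF alone gave 0.085 at 25% v 5% and 0.131 at 40% v 10%.

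**LOCF bias under the null, by hand.** Let p be the dropout in an arm. Half the dropouts lose the full 10 points; the other half lose 10 - 7 = 3. The mean gain therefore falls by (p/2) x 10 + (p/2) x 3 = 6.5p.
- 25% v 5%: 6.5 x 0.20 = 1.30 points (simulated 1.25).
- 40% v 10%: 6.5 x 0.30 = 1.95 points (simulated 1.89).

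The other three methods stayed within 0.1 point of zero.

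**LOCF when the effect is real.** Take a true difference of 10 points at T2 (7 at T1) and 40% dropout in both arms. The LOCF estimate is 10 - 0.20 x 10 - 0.20 x (10 - 7) = 7.4 points, with simulated power 0.70. The other three methods stay near 10 points with power 0.89-0.92. The choice of method can thus move the result in either direction.

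**The case against.** The paragraph is better than its worst sentence. It puts plausibility of assumptions first, which is a criterion that does not depend on the data. It warns about unequal missingness, and it keeps all randomised participants in the sensitivity analysis. It speaks of comparing methods and does not literally say that results are compared. Nothing in it says that the best method means the most favourable one. The analyst is independent of recruitment, assessment and intervention. At the only dropout rates the article cites, the worst-case excess is roughly 1.5 to 3 percentage points.

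Most of this stands as mitigation, and it limits the size of the point. It does not remove it. Plausibility is a principle that ranks none of the four methods. Independence from trial conduct is not masking to arm when the method is chosen. A separate SAP might name a method, but the protocol itself states the selection rule, so the SAP would have to override it.

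Three stronger readings are tempting and not supported:
- **Covariates triggered by imbalance in the primary model.** The sentence "However, if important differences are found, regression analysis will be used to evaluate these data to estimate the effects of covariates" belongs to the description of baseline characteristics and is not said to alter the primary model. The ANCOVA with baseline as covariate is set separately and without condition.
- **A switch that drops baseline adjustment.** "Non-parametric tests will be performed if some of the outcomes do not meet the conditions necessary for parametric analysis" is a generic fallback that follows the sentence on secondary outcomes. It names no test, so loss of adjustment would be inference.
- **Type I error of 14-17%.** That figure arises when any of the three change-score contrasts may count as well. With no missing data and one method, the three contrasts alone already give about 12%. That is mostly a separate multiplicity question.

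**Conclusion.** The point holds in a limited form. The protocol fixes a rule under which the primary missing-data method is chosen late, on a criterion it does not make operational, from a list that includes LOCF and complete case. It affects the primary outcome and, through the shared strategy, the secondary ones.

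The size is modest if dropout is low and equal: about 6-8% in place of 5% at the cited 7.5-14%, and about 9% at 40%. These are upper bounds, because they assume the most favourable method is kept. The larger figures, a spurious 1.3-1.9 points and a type I error of about 8-13% for LOCF alone, need unequal dropout of 25% v 5% or 40% v 10% and a gain of about 10 points in both arms. Neither condition is stated in the article, which uses 10 points as the difference to be detected. A reader might infer that the plan intends to pick the most favourable result. The text leaves that possible but does not say it.

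**What to change.** Delete the sentence that says the best strategy will be chosen. Before unblinding, in a dated amendment, name one primary method covering all randomised participants under missing-at-random. Either of these would do:
- multiple imputation with MICE, already planned, followed by the stated baseline-adjusted ANCOVA; or
- a likelihood-based model using the Barthel index at T0, T1 and T2.

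Report the other listed methods only as sensitivity analyses that cannot replace the primary, and state that LOCF is never eligible as primary. Reword the last clause of the paragraph so that all randomised participants belong to the primary analysis too.

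The cost is a little analysis work and the loss of freedom to choose later. Both options are already on the protocol's list, and no change to sample size or data collection is needed. Trial status reports 40 participants randomised by the end of December 2015, so the amendment should be made promptly.

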The effectiveness of stroke interventions is often described by measures of disability, or functional assessment. Evaluations that deal with activities of daily living (ADLs) generally include the Functional Independence Measure, the Katz index and the Barthel index (BI), the latter being a prevalent measure for the clinical evaluation of stroke patients, with substantial supporting research [26–28]. However, there are few studies involving the ADLs as the primary outcome for a marker of functional recovery after neurostimulation. For example, in a systematic review where the efficacy of tDCS in ADLs and motor function after stroke were analyzed, the authors found that the results are inaccurate and the effect was not sustained when studies of high methodological quality were included. There were 15 studies involving a total of 455 participants included, with only randomized controlled trials and randomized controlled cross-over trials evaluated. Of the total, the analysis of five studies involving 286 participants to examine the effects of tDCS on our primary outcome (ADLs evaluated by BI) has shown that no effect was observed on the performance at the end of the intervention. In three studies from this systematic review involving 99 participants to evaluate the effects of tDCS in BI scores at the end of follow-up, evidence suggested an effect on the ADL performance, but the confidence intervals were wide, and the effect was not sustained when they only included studies with low risk of bias. Thus, the authors point to the need for future research in this area to improve the generalization of the results [29].

Although clinical trials can be found that measure the efficacy of tDCS in ADLs pointing to positive effects [30, 31] among other factors, in general they only include participants in the chronic stage with brain injuries in different areas and varying levels of functional incapacity.

Therefore, central questions remain: For a daily protocol of 10 days, does the active tDCS applied under a 2 mA current and associated with CIMT have a superior response to the simulated (placebo) current applied with CIMT, and if so, what is the size of the effect? What adverse effects are associated with the therapy? Does functional improvement in the ADLs persist over time?

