### Outcomes

For analysis of the primary endpoint, the Barthel index (BI) was chosen because it is commonly used in studies related to post-stroke rehabilitation, adequately reflecting clinical practice [47–49]. This instrument is designed to assess the patient’s level of independence to perform ten basic life activities: eating, bathing, personal care, ability to dress themselves, motility, urinary regularity, bathroom use, chair-bed transfer and vice versa, mobility, and climbing stairs [50]. The literature on the minimal clinically important difference detected by the BI shows that a change of 2 points is meaningful and beyond measurement error. This calculation refers to a modified BI with scores of 0–20 points [51]. Since the changes in the values of the scores do not affect other properties of the scale, it is considered equivalent to the original version, with scores of 0–100 points [52]. Thus, taking the original scale used in this study as a reference, clinical improvement will be considered as a final score higher than 10 points (T2) according to the BI, compared to baseline (T0) before the therapeutic protocol [30].

The BI has been reported with excellent levels of reliability, validity, and adequate responsiveness to change in several countries [52, 53]. In a study of 121 patients at four post-stroke period points (14, 30, 90, and 180 days), the inter-rater reliability using a weighted kappa varied from 0.53 (adequate) to 0.94 (excellent). The inter-rater reliability for the total score, calculated using the intraclass correlation, was 0.94 (excellent). The internal consistency, calculated using Cronbach’s alpha, was excellent, varying between 0.89–0.92 [54]. The construct validity was also confirmed by Wilkinson et al. [55], with rank correlation coefficients of the BI with the SF-36 (Medical Outcomes Study 36-item Short-Form Health Survey) subscales being found in patients with their first-ever stroke varying from r = 0.22 (Role Emotional subscale) to 0.81 (Physical Functioning Profile subscale).

Secondary outcome measures include the Modified Ashworth Scale, the 30-item Motor Activity Log, the Biodex Balance electronic platform, the Postural Assessment Scale for Stroke, the Falls Efficacy Scale, the Medical Research Council scale, the Short Physical Performance Battery, the Wolf Motor Function Test, and the SF-36.

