### Sample size

The sample size was estimated based on previous studies using matched groups of non-invasive stimulation with rehabilitation [98, 99]. The power calculations to determine the number of participants in each group were determined in relation to the expected change in BI because it is commonly used in tDCS studies of patients after stroke [30, 31].

According to Khedr et al. [30], the mean expected improvement is about 10 points, with a standard deviation (SD) equivalent to 7 points. Thus, a calculation considering 90 % power suggests that it would take at least 12 patients in each group to detect the difference found corresponding to the effect of active or placebo tDCS.

Considering the possibility of sample loss during the study (withdrawal, inability to continue the treatment, mortality), 20 patients will be included per group, totaling 40 participants (SPSS Ver.20.0; SPSS Inc., Chicago, IL, USA). The analysis will be performed at a 0.05 significance level.

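### The only effect estimate and confidence interval named is a standardised difference in change scores, not the estimate from the baseline-adjusted ANCOVA that tests the groups, so interval and test can disagree

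*Protocol article*

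**What the plan says.** All of this is in the Data analyses section of the protocol article unless noted.

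- Outcome: "the primary outcome will be analyzed with analysis of mean change scores (MCS) to the total score of BI", for T1-T0, T2-T0 and T2-T1.
- Test: "The baseline as covariate will be used to identify potential differences between the groups by analysis of covariance (ANCOVA".
- Estimate: "the effect sizes and confidence intervals of change scores will be calculated", as Hedges-corrected Cohen's d, "with values of 0.20, 0.50, and 0.80, reflecting small, medium, and large effects, respectively".
- Scope: "For all variables of the secondary outcomes, the same analysis strategy will be used".

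The Background section lists "what is the size of the effect" among the trial's central questions. The Sample size section adds "The analysis will be performed at a 0.05 significance level", without giving sidedness. Nowhere does the article name a between-group difference in BI points with an interval, say whether d uses the raw or the adjusted difference, or say which SD is the divisor.

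**The concern.** A p-value and an interval reported for the same comparison should come from the same model. Here the p-value comes from a model that uses baseline, while the interval is defined on change scores with no stated link to that model. A d on raw change fixes the baseline slope at 1; ANCOVA estimates it. With 20 per arm, chance baseline imbalance separates the two, and the change-score version discards precision that the planned model already provides.

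The report could therefore show a significant primary test beside an interval that includes zero, or the reverse, with no rule for which answers the effect-size question. The verbal label adds a further uncertainty, because it changes with the divisor.

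**Working it through.** **The plan's own figure.** Inputs from the Sample size section: difference 10, SD 7, 90% power, alpha 0.05 (two-sided assumed). The normal formula gives 2 × (1.960 + 1.282)² × (7/10)² = 10.3, so 11 per group. With the t distribution, power is 0.890 at 11 and 0.917 at 12. The stated 12 per group is reproduced. At 20 per group, power is 0.993.

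**Why the two estimates differ.** Let Dx be the between-group difference at baseline, Dy the difference at follow-up and b the within-group slope.

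- Raw change: Dy − Dx
- ANCOVA: Dy − b·Dx
- ANCOVA minus raw change: (1 − b)·Dx

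Dx averages zero under randomisation, so this gap has no systematic direction.

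**Precision.** With equal SDs at both visits and pre-post correlation r, SD(change)/SD(raw) = √(2(1 − r)) and SD(residual)/SD(raw) = √(1 − r²). Their ratio is 1.24, 1.15, 1.08 and 1.03 at r = 0.3, 0.5, 0.7 and 0.9. That is roughly how much wider the change-score interval is.

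**Disagreement on significance.** The simulation used 20 per arm, normal scores, equal SDs and 40,000 trials per setting. The change-score interval was judged by the matching t-test. The document does not give r, so it was varied. True effect 0.5 raw SD:

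| r | Power, ANCOVA | Power, change | Disagree | ANCOVA only significant | Change only significant |
|---|---|---|---|---|---|
| 0.3 | 0.357 | 0.256 | 19.6% | about 15% | about 5% |
| 0.5 | 0.415 | 0.339 | 17.5% | about 13% | about 5% |
| 0.7 | 0.568 | 0.514 | 13.8% | about 10% | about 4% |
| 0.9 | 0.936 | 0.930 | 2.6% | about 2% | about 1% |

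The last two columns follow from the others: ANCOVA only = (disagree + difference in power)/2, for example (0.196 + 0.101)/2 = 0.149, and the remainder is change only. With no true effect, disagreement is 5.4% to 2.3% across the same correlations. With a true effect of 0.8 raw SD it is 23.5%, 16.2%, 6.2% and 0.0%.

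If 7 is the SD of change, an effect of 0.5 raw SD at r = 0.3, 0.5 and 0.7 is 0.423 × 7 = 3.0, 0.5 × 7 = 3.5 and 0.645 × 7 = 4.5 BI points.

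**At the planned effect.** d = 10/7 = 1.43. The change-score test misses in only 1 − 0.993 = 0.7% of trials with 20 per arm, so there is little room for conflict.

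**Label.** Mean standardised effect for the same true effect of 0.5 raw SD, by divisor:

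| r | Raw change / change SD | Adjusted / change SD | Adjusted / residual SD | Adjusted / baseline SD |
|---|---|---|---|---|
| 0.3 | 0.423 | 0.424 | 0.526 | 0.501 |
| 0.5 | 0.499 | 0.499 | 0.576 | 0.499 |
| 0.7 | 0.648 | 0.647 | 0.702 | 0.501 |
| 0.9 | 1.118 | 1.118 | 1.147 | 0.500 |

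Against the baseline-SD version, the change-score label is higher in 15.1% and lower in 32.2% of trials at r = 0.3, but higher in 43.4% and lower in 4.9% at r = 0.7. Against the residual-SD version it is more often lower: 35.6% against 12.4% higher at r = 0.3, and 20.6% against 7.7% at r = 0.7.

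**The case against.** The best defence is that the article does not say *unadjusted*. The sentence on d follows the one that makes change the ANCOVA outcome, so it may name only the variable, and a condensed article may leave the derivation of d to a fuller plan. The mean change analysis is in BI points, and d comes last, as an addition. At the planning values both methods should agree.

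Part of this stands. *Unadjusted* is the natural reading, not the written one, and conflict is unlikely at the planned effect. But the article does not merely omit a detail: it specifies an estimator, an interval and label cut-offs, and none is tied to the model used for the test. Effect size is one of its own questions, and the same strategy covers every secondary score, for which no planned effect is given.

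Three stronger readings may tempt a reader, and the document does not support them.

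- *The effect will be labelled larger than it is.* This needs the baseline SD as comparator and a correlation above 0.5; the document gives neither. With the change SD there is no average shift, and with the residual SD the planned d is the smaller one. At the planning values, with 7 as the change SD, d on the raw SD is 1.69, 1.43, 1.11 and 0.64 at r = 0.3, 0.5, 0.7 and 0.9, and stays in the large band until r exceeds about 0.84.
- *The two estimates may differ by several BI points.* Assuming a baseline SD of 15-20 and slope of 0.6-0.8, the 95% range of (1 − b)·Dx is 1.96 × (1 − b) × SD × √(2/20), or 1.9 to 5.0 points. If instead the article's SD of 7 is the SD of change, the same baseline SDs imply r of about 0.89-0.94 and a range of only 0.8-1.0 points.
- *The group difference should be read against 10 points.* The Outcomes section says "clinical improvement will be considered as a final score higher than 10 points (T2) according to the BI", compared with the patient's own baseline. That is a within-patient criterion, not a threshold for a difference between group means.

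**Conclusion.** The point holds as a mismatch between test and estimate, with no fixed direction. If d is computed on raw change, its interval is less precise than the ANCOVA estimate and, at 20 per arm with a true effect of 0.5 raw SD, contradicts the test on significance in about 14-20% of trials for correlations of 0.3-0.7 and about 3% at 0.9. These figures rest on normal scores, equal SDs at both visits, a two-sided 0.05 level and an assumed correlation. The label is undetermined until an SD is named, and could come out higher or lower.

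The validity of the primary test is not in question, and the stated sample size is reproduced. The weakness concerns how the size of the effect is reported, mainly for moderate effects and the secondary outcomes. It is worth correcting because the better estimate is already an output of the planned model.

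**What to change.** State that the between-group difference in BI points from the ANCOVA with baseline as covariate, with its 95% CI, is the main effect estimate. Do the same for each secondary score in its own units wherever ANCOVA is used. If a standardised effect is kept, divide that adjusted difference by an SD named in advance, apply the Hedges correction, and state the divisor beside the result. The pooled baseline SD is one option, and in the simulation it did not vary with the correlation, but nothing in the document requires it. Do not judge the group difference against the within-patient 10-point criterion.

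The cost is one sentence and no new analysis. The standardised figure may change and will be less directly comparable with published change-score values; a raw-change d can be kept as a labelled supplement. The Trial status section reports 40 participants already randomised, so the change should be dated before group codes are linked to outcomes.

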The Modified Ashworth Scale, used in semiotic clinics for spasticity evaluation, evaluates the tone in grades of 0-4 points, and is widely used in clinical practice with adequate test-retest and inter-rater reliability [56–58].

The 30-item Motor Activity Log measures the spontaneous use of the affected limb. Each item asks about the frequency and quality of movement in daily activities of the paretic upper limb. Scores on this measure have adequate reliability and validity in individuals with stroke [59, 60].

The Biodex Balance electronic platform measures the static and dynamic balance through different levels of stability, such as anteroposterior and mediolateral. This instrument is used in several studies involving tDCS applied to stroke [61, 62].

The Postural Assessment Scale for Stroke (PASS) for postural control [63] contains 12 items with progressive levels of difficulty, involving three fundamental postures (lying, sitting, and standing).

The Falls Efficacy Scale measures the fear of falling in 16 ADLs. The total score can vary from 16 (no concern) to 64 (extreme concern) [64, 65].

The force scale from the Medical Research Council (MRC) consists of manual muscle testing, varying from 0 (no movement is observed) to 5 (normal force against the total resistance), with a maximum score of 60 points [66].

The Short Physical Performance Battery (SPPB) consists of three tests that evaluate the static standing balance, gait speed in normal step, and, indirectly, the muscle strength of the lower limbs. Each domain varies from 0 to 4 points, and the maximum total score indicates better physical performance [67, 68]. Gait velocity is a relevant indicator of function and prognosis after stroke [69], meaning that the SPPB is an important tool for assessment of lower extremity motor recovery [70–72].

The Wolf Motor Function Test (WMFT) assesses the speed of task execution through time, the quality of movement, and the strength of grip and shoulder flexion in specific tasks. The WMFT tasks should be filmed with a camera placed at standard position and distance, and the score of the tasks are given from video analyzes [73, 74].

The SF-36, a multidimensional questionnaire to analyze the state of health, consists of 36 items encompassing 8 components, with a final score of 0 (worst state) to 100 (best state) [75].

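### The non-parametric fallback does not keep the baseline covariate; on the usual reading, the adjustment is lost on the bounded or ordinal scales where the switch could well be used

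*Protocol article*

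**What the plan says.** The Data analyses section of the protocol article analyses the Barthel index total through mean change scores (T1-T0, T2-T0, T2-T1) and states: "The baseline as covariate will be used to identify potential differences between the groups by analysis of covariance (ANCOVA". The same strategy is extended to all secondary outcomes. The section then gives one exception: "Non-parametric tests will be performed if some of the outcomes do not meet the conditions necessary for parametric analysis". It does not name the test or the check that triggers it. It also does not say whether the test is applied to change or final scores, or whether baseline stays in the comparison.

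The Outcomes section shows which measures the exception could reach. The Barthel index is a 0-100 total over ten activities. The Modified Ashworth Scale "evaluates the tone in grades of 0-4 points". MRC strength is graded 0-5, and each SPPB domain runs from 0 to 4.

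The Sample size section supplies the design figures: "the mean expected improvement is about 10 points", "with a standard deviation (SD) equivalent to 7 points", "considering 90 % power" and "it would take at least 12 patients in each group", raised to 20 per group to allow for losses. It adds: "The analysis will be performed at a 0.05 significance level".

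**The concern.** The exception replaces a baseline-adjusted model with a class of tests whose common members (Mann-Whitney, Wilcoxon) take no covariate. Whether an outcome is compared with or without adjustment would then depend on how the trial data look, although the functional assessments are scheduled at T0 for every patient.

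A change score is not a full substitute. It fixes the coefficient of baseline at 1, whereas ANCOVA estimates it. On a bounded scale, patients who start high also have less room to improve than patients who start low.

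With 20 patients per arm and no stratification described under Randomization and blinding, the baseline value is the obvious source of precision and of protection against chance imbalance. What is at stake is mainly power, more for the secondary scales than for the primary outcome as it was sized.

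**Working it through.** **Inputs.** From the Sample size section: difference 10, SD 7 (taken as the SD of change), alpha 0.05 (taken as two-sided), 12 needed and 20 planned per group. From the Data analyses section: the benchmark of 0.80 for a large effect, which on this SD is 0.80 × 7 = 5.6 points. Assumed, because the article gives none: baseline/follow-up correlation ρ of 0.3, 0.5 or 0.7, with equal SDs at both times.

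**The plan's own figure.** The normal approximation gives n = 2(1.960 + 1.282)² × 7² / 10² = 10.3, so 11 per group. The exact two-sided t-test has 89.0% power at 11 and 91.7% at 12. The stated 12 per group is reproduced.

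**Why adjustment gains precision.** If the SD of change is 7, the SD at each time is s = 7/√(2(1−ρ)). The residual SD after adjusting for baseline is s√(1−ρ²) = 7√((1+ρ)/2). For ρ = 0.3, 0.5 and 0.7 this is 5.64, 6.06 and 6.45, against 7 for raw change. The adjusted variance is therefore 65%, 75% and 85% of the unadjusted one. For T1-T0 and T2-T0, ANCOVA with the T0 value as covariate gives the same group comparison whether the response is the change or the final score.

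**Power on unbounded normal data**, by simulation, two-sided 0.05. Entries are for ρ = 0.3 / 0.5 / 0.7.

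| Setting | Rank test on change | ANCOVA | Loss (points) | Rank ANCOVA |
|---|---|---|---|---|
| 20 per group, 10 points | 99% | over 99% | about 1 | over 99% |
| 12 per group, 10 points | 89% | 98 / 96 / 94% | 9 / 7 / 5 | 97 / 95 / 91% |
| 20 per group, 5.6 points (d = 0.80) | 67% | 85 / 80 / 75% | 18 / 13 / 8 | 84 / 77 / 70% |

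Part of the loss comes from ranking rather than from the missing covariate. At 12 per group and 10 points, the unadjusted t-test on change has 91.7% power and the rank test 89%, so nearly 3 points belong to ranking.

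**Power on a bounded scale.** Scores were rounded to steps of 5 and clipped at 0-100, with an average gain of 10 before clipping in the control arm, 20 per group and a 10-point effect. The baseline means are assumptions.

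- Baseline mean 60: the rank test on change loses about 1 point against ANCOVA.
- Baseline mean 80: rank test 94 / 90 / 83%, ANCOVA 100 / 99 / 98%. The loss is about 6 / 9 / 15 points. Rank ANCOVA matches ANCOVA.

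On these bounded scores with no true difference, ANCOVA and rank ANCOVA both rejected close to 5% of the time.

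**The case against.** The strongest reply is that the article never says the covariate is dropped. Rank ANCOVA is a non-parametric method and would fit the wording, and a condensed article may leave the name of the test to an analysis plan that is not shown. This stands as far as it goes: a reader might infer that the plan states an unadjusted analysis, and it does not. What remains is that the only stated rule sets parametric analysis against non-parametric tests and carries nothing over from the ANCOVA. The ordinary reading of that is a rank test of two groups.

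Second, at the design as planned the loss is about 1 point. This also stands. The larger figures need either attrition down to 12 per group, a smaller effect, or baseline scores near the ceiling. The 0.80 benchmark appears in the plan only as a label for interpreting effect sizes, and no secondary outcome is powered.

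Third, normal-theory ANCOVA may be an unfair benchmark when its conditions are judged to have failed. The bounded-scale check answers this for the settings tried: ANCOVA kept its level and did at least as well as the rank test on change. The proposed alternatives do not need normality in any case.

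Fourth, the plan provides for regression on covariates if important baseline differences are found, and change scores already subtract baseline. Both soften the exposure to imbalance. The first is itself conditional on the data, and the second is not equivalent to adjustment, as the variance ratios show.

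A reader might also infer that the switch is bound to be used, or that it inflates the type I error. The article gives no trigger, so use is plausible rather than certain. The error rate of the two-stage procedure was not computed, so no inflation is claimed.

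**Conclusion.** The point holds as a weakness in a stated rule. Every outcome starts with a baseline-adjusted comparison, and any outcome that fails the parametric conditions goes to an unnamed test without a provision to keep baseline.

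The size is conditional. With ρ assumed between 0.3 and 0.7, the primary outcome at 20 per group, 10 points and SD 7 loses about 1 point of power away from the ceiling. The loss is about 5 to 9 points if 12 per group remain, and about 8 to 18 points for an outcome with d = 0.80 at 20 per group. It is larger near the ceiling: about 6 to 15 points for the primary effect at an assumed baseline mean of 80. A single unconditional loss of several points, applied to the planned primary analysis, would overstate the case; the plan's own inputs do not support it.

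The correction is worth making because it is cheap and because the secondary scales, which are not powered, have the most to lose.

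**What to change.** Reword the fallback so that the baseline-adjusted comparison is kept for every outcome, and state in advance what is done when parametric conditions fail:

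- a permutation (re-randomisation) p-value for the same ANCOVA, or rank ANCOVA;
- for short ordinal scales such as the Modified Ashworth, a proportional-odds model with the baseline value as covariate;
- any unadjusted rank test of change scores reported only as a sensitivity analysis.

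Name the check that triggers the switch in the same sentence.

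The cost is analysis wording and slightly more programming. The baseline assessments are already scheduled and R is already among the named software. One limit should be known: on unbounded data with a correlation near 0.7, rank ANCOVA gains only about 1 to 3 points over the unadjusted rank test (91% against 89% at 12 per group and 10 points; 70% against 67% at d = 0.80 and 20 per group). The permutation version of the ANCOVA is therefore the better default for scores with many levels.
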